### 2.8. Director Assessments

The *Director Program Sustainability Survey* is based on an existing tool [40] and measures factors associated with program sustainability including ECEC administration, policies, and procedures. Specifically, questions focus on the type of ECEC (e.g., for-profit vs. non-profit), the number, types, processes, and rules for meals served at the ECEC; current physical activity and nutrition training offered to staff at the ECEC as well as future training needs; use of best practices for physical activity and nutrition at the ECEC as well as barriers/facilitators to using those practices; and ECEC directors’ communication with parents. Directors complete this survey prior to and following implementation of SAGE. The 38 questions on this survey consist of check-all that apply, multiple choice, fill in the blanks, and Likert-type scale questions. Responses from baseline to post-intervention will be compared to evaluate the impact of the SAP on outcomes.

The *Sustainability Needs Assessment* (SNA) is based on an existing tool [1] and completed by the ECEC director during SAGE week 3 and SAGE week 10. This assessment allows the director to rate the SAGE program on five RE-AIM dimensions: reach, efficacy, adoption, implementation, and maintenance [45]. Each RE-AIM dimension is evaluated using 6–10 questions (37 total), which are scored using a five-point Likert-type scale: (1) strongly disagree, (2) disagree, (3) neither agree or disagree, (4) agree, and (5) strongly agree. The SNA also investigates process factors associated with implementing the new program such as the perceived feasibility of the study design, the center setting, and the community environment (e.g., having the space and resources available to support the program). Responses from baseline to post-intervention will be compared to evaluate the impact of the SAP on SAGE’s perceived RE-AIM characteristics.

### 2.9. Parent Assessments

The *Newsletter Survey* asks parents to evaluate the newsletters and sustainability of SAGE processes. Specifically, the survey includes seven questions that assess SAGE-related parent-teacher and parent-child interactions, the frequency of receiving, value, and preferred aspects of the newsletters, and overall impact of the SAGE program on their child. The survey also contains a space for parents to write testimonials (if applicable) about positive or negative aspects of SAGE.

### 2.10. Environmental Assessments

Three validated *Nutrition and Physical Activity Self-Assessment for Child Care (NAP SACC)* [46] environmental assessments at each ECEC will be used to measure the quality of resources related to physical activity, nutrition, and screen time. Evaluations used a combination of direct observation by research staff, self-report by teachers, and self-report by directors to measure outcomes. About two weeks before the start of the programming (either SAGE Garden or Child Safety), a research team member assesses outdoor play environment quality, ECEC teachers reported on the indoor environment, and the ECEC director reported the quality of physical activity, nutrition, and screen time policies. This 24-item assessment consists of check all that apply and Likert-type scale questions. For a further description of the assessment process, see Szeszulski et al., 2022 [47]. Responses from baseline to post-intervention will be compared to evaluate the impact of the SAP and SAGE on physical activity, nutrition, and screen time environments.

The *Physical Activity Resource Assessment (PARA)* is an established direct observation checklist [48] that is completed by SAGE staff on site at each ECEC two to three weeks before the start of programming. This assessment consists of fill in the blank, multiple choice, yes or no, and Likert-type scale questions. Questions focus on the availability of physical activity features such as sports fields, play equipment, and trails, amenities such as water fountains, lighting, and shade, and incivilities such as broken glass, graffiti, and vandalism. This 45-item assessment takes about 10 min to complete. Responses from baseline to post-intervention will be compared to evaluate the impact of the SAP and SAGE on the physical activity environment.

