## 2. Method

### 2.1. SAGE Overview and Design

SAGE uses a garden-based curriculum to increase physical activity and improve fruit and vegetable consumption in young children, age 3-to-5 years old, at 24 ECECs to help meet national policy guidelines for ECECs [35]. As previously described, SAGE follows the EMO framework and is implemented in ECECs focusing on *micro-level* environmental changes by installing a garden and working with center directors to guide evidence-based ECEC policy choices. At the *meso level*, teacher training and support is used to deliver an enhanced garden-based curriculum to meet *macro-level* ECEC standards for obesity prevention and early education. Parents are engaged using weekly newsletters linked to garden and classroom activities to enhance *exo-level* transfer of benefits [33].

SAGE includes active learning games and songs that use the plant life cycle as a metaphor for human development. Children and teachers complete garden maintenance and exploration time as a part of the curriculum and to promote garden sustainability. Other curricular activities include three science experiments, mindful eating exercises (“tummy mindfulness”) to sample new fruits and vegetables, and interactive discussion time to reinforce content. All activities are designed to align with National Association for the Education of Young Children (NAEYC) teaching standards.

Garden locations are selected with ECEC directors, maintenance staff, and teachers involved with the delivery of SAGE. If a garden exists already but is not used, efforts are made to breathe new life into the existing build or, if it is not well sited (e.g., inadequate or excessive sun exposure, inadequate drainage), to relocate it. SAGE gardens are sized to maximize access for young children (4’ × 6’) and built using inexpensive, and widely available materials (cinderblocks, soil, trellises). CAB members, teachers, and SAGE staff work together to build the garden. Planting seeds and seedlings is incorporated into the curriculum so that children can participate in this activity. See the garden build protocol in Supplementary File S1.

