### 2.3. SAP Rollout Process

The SAP commences before the curriculum begins and unfolds in a five-step process, which is also described using the plant life cycle as a metaphor. Figure 2 depicts this process and is color coded by stakeholder. Step 1 focuses on planting the idea of sustainability. Steps 2 and 3 focus on reinforcing and growing interest in the concept of sustainability. Steps 4 and 5 empower ECEC staff to sustain SAGE and transition responsibilities and resources associated with SAGE to the ECEC and community.

*SAP Step 1*. *Planting the seeds: Organizational assessment and training (Pre-Implementation).* Prior to implementation, SAGE staff will meet with teachers and ECEC directors to deliver curriculum supplies and conduct an initial training. This training introduces the PRIME principles (described above), provides a brief overview of the curriculum, and gives the ECEC staff a tour of the garden where they have an opportunity to plant seeds as part of the garden introduction. Fresh fruits and vegetables that represent what might be served as part of the curriculum are sampled during this meeting, and several songs and games demonstrated and played with center staff. During all activities, SAGE staff emphasize how the curriculum can fit within current teaching practices and connect activities to NAEYC standards.

*SAP Step 2. Weed control: Identification of challenges (weeks 1–3).* Once ECEC personnel begin to have some experience implementing SAGE, an assessment will be administered to ECEC directors to investigate process factors associated with implementing the new program. Teachers also complete a self-evaluation. Data from all assessments will be reviewed and used to develop the booster training session in SAP Step 3.

*Step 3. Nurturing the seedlings: Overcoming challenges (weeks 4–5)*. Challenges identified in the assessments will be presented to the CAB, ECEC directors and teachers, and the scientific team to allow all parties to develop a shared vision of how SAGE might be replicated in future classrooms. This step also nurtures community capacity by improving evidence-based knowledge about meeting health behavior guidelines and education standards, improves the potential for continuation of benefits to children as they develop, and identifies current and future resources and changes needed to promote institutionalization of SAGE.

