### 2.7. Teacher and Director Assessments

*SAGE Self Efficacy Assessment* is an assessment specifically developed for SAGE that is administered to teachers and directors at the teacher training (two to three weeks before start date), the end of the “see one” phase of SAGE (week 5), at the end of the “do one” phase of SAGE (week 10), and following program delivery. This questionnaire includes five statements that staff respond to using a five-point Likert-type scale: (1) strongly disagree, (2) disagree, (3) neither agree or disagree, (4) agree, and (5) strongly agree. Statements ask how confident staff are that they continue to care for and maintain the garden, allow children to water and interact with the garden weekly, provide children with active songs, games, and discussions from the SAGE curriculum weekly, provide children with the mindful eating experience with fresh fruits and vegetables weekly, and engage parents and other community members in SAGE. Averages across all five questions are calculated by staff type (i.e., director vs. teachers) and for each ECEC. Changes or patterns in self-efficacy will be tested to determine whether they mediate changes in other sustainability constructs (e.g., ECEC health environments).

*Interviews.* Exit interviews with ECEC directors, teachers, and other engaged staff (e.g., kitchen personnel, teacher aids) will be conducted after implementation has been completed to investigate factors impacting sustainability along the dimensions of child learning, teacher acquisition of skills needed to deliver the SAGE curriculum, and ECEC achievement of policy guidelines and project milestones. Interview data can be used to inform scaling up SAGE for broader deployment if it is successful in meeting its goals or modifying SAGE if some pieces are unsuccessful. Semi-structured interviews are iterative in nature, taped, transcribed, and analyzed using thematic content analysis. Emergent themes will be identified using a constant comparison approach [41,42,43,44].

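### Baseline PARA and outdoor NAP SACC are timed from the start of programming, not from the garden build, so the measured change may leave out garden installation

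*Protocol article*

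**What the plan says.** Here SAP means the Sustainability Action Plan.

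- **Baseline PARA (section 2.10):** "completed by SAGE staff on site at each ECEC two to three weeks before the start of programming".
- **Baseline NAP SACC (section 2.10):** "About two weeks before the start of the programming (either SAGE Garden or Child Safety), a research team member assesses outdoor play environment quality". Teachers report on the indoor environment and the director on policies.
- **Use of both (section 2.10):** baseline and post-intervention responses are compared, and the difference is read as the impact of the SAP and SAGE on these environments.
- **Initial training (section 2.3, Step 1):** it takes place before implementation and "gives the ECEC staff a tour of the garden where they have an opportunity to plant seeds as part of the garden introduction".
- **Date of the training (section 2.7):** the self-efficacy assessment is first given "at the teacher training (two to three weeks before start date".
- **What SAGE changes (section 2.1):** the micro-level work consists of "environmental changes by installing a garden" and of working with directors on policy choices.

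The article gives no date for the garden build. Section 2.1 refers to Supplementary File S1 for the build protocol, and that file is not at hand.

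**The concern.** A before-after comparison measures an intervention only if the first observation comes before it. Section 2.10 fixes the first observation relative to the first curriculum session. The physical part of SAGE, the garden, has to exist before that session, and the dated events suggest that it exists by the time the baseline is taken.

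At a centre where the baseline follows the build, the garden is in both the first and the second score and cancels out of the difference. Whatever it adds to the score is then lost from the estimated effect. Later analysis cannot repair this, because a pre-build observation that was not made cannot be recovered.

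**Working it through.** The article gives no figure to reproduce. The check sets the dated events on one time line, with week 0 as the start of programming.

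| Event | Time | Source |
|---|---|---|
| Initial training | weeks -3 to -2 | section 2.7 |
| Garden tour and planting | at that training | section 2.3, Step 1 |
| Baseline PARA | weeks -3 to -2 | section 2.10 |
| Baseline NAP SACC, outdoor part | about week -2 | section 2.10 |
| Garden build | no date given | section 2.1 |

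**Step 1. Sections 2.3 and 2.7 describe the same training.** Section 2.2 lists one training before implementation (90 minutes) and one booster about five weeks in. The pre-implementation training of section 2.3 and the training dated in section 2.7 are therefore the same event.

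**Step 2. Latest date for the garden.** Staff tour the garden and can plant in it at the training, so it is on site by then, at weeks -3 to -2.

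**Step 3. Outdoor NAP SACC.** Let the training fall T days before the start, with T between 14 and 21. An observation exactly 14 days before the start falls on or after the training, and so after the build, whatever T is. The word *about* leaves some room. If T is uniform over the 7 days, the build ends on training day, and the observation is d days earlier than day 14, the share of centres observed after the build is (7 - d)/7. Each day earlier takes off 1/7, or 14 percentage points. The order is probable but not certain.

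**Step 4. PARA.** The PARA shares the training's window, so the documents do not settle the order. For illustration, assume that the PARA and training dates are independent and uniform over the 7 days, and that the build ends L days before the training. Then

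share of PARA baselines after the build = 1 - ((7 - L)/7)² / 2

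- L = 0: 1 - 1/2 = 0.50
- L = 3: 1 - (4/7)²/2 = 1 - 0.163 = 0.84
- L = 7: 1 - 0 = 1.00

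The values of L are assumptions; none is in the article. Staff who run both activities could also order them deliberately, and independence would then fail.

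**Step 5. Effect on the estimate.** Let g be what a garden adds to a centre's score, and s the share of SAGE centres whose baseline follows the build. The mean change then omits s × g. Steps 3 and 4 concern s only. The article gives no basis for g: the PARA features, amenities and incivilities it gives as examples do not include a garden, and its summary of the NAP SACC names no garden item. If g is zero, nothing is lost. If g is positive, the change is understated.

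**The case against.** The strongest reply is that the order of build and baseline is an operational detail. It may be settled in Supplementary File S1 or in the separate paper to which section 2.10 refers for the assessment process. This stands as a limit on certainty, but the article itself fixes the baseline times, and the times it fixes allow, and for the outdoor NAP SACC favour, a baseline after the build.

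Three further replies also stand. The garden may add little to either score. The indoor and policy parts of the NAP SACC are not altered by installation itself, so change in policy remains measurable. The problem is also not uniform: the NAP SACC is taken before Child Safety as well, where no build is described, and section 2.1 allows for centres that already have an unused garden.

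Several stronger readings are tempting, and the document does not support them:

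- *The baseline is scheduled with the garden already in place.* No section says so. It is an inference from overlapping windows, probable for the outdoor NAP SACC and open for the PARA.
- *The comparison misses the main environmental change.* Section 2.1 names two micro-level components and does not rank them.
- *Micro-level institutionalization rests on these two instruments.* Table 1 lists five measures in that cell. The others are the Director Program Sustainability Survey, the Teacher Self-efficacy Assessment and the Sustainability Needs Assessment.
- *A baseline-adjusted comparison with Child Safety would be biased too.* Section 2.10 describes only a baseline-to-post comparison, so this would concern an analysis that the article does not state.

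**Conclusion.** The point holds as a weakness in how the baseline is defined. At centres about to receive SAGE, the outdoor NAP SACC baseline probably follows the garden build and the PARA baseline may. The change credited to the SAP and SAGE may therefore omit garden installation, and any resulting error is an understatement.

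This rests on three things: sections 2.3 and 2.7 describe the same training, the garden toured there is the SAGE garden, and a garden raises the scores at least somewhat. The last cannot be checked from the article, so no size can be given for the understatement. The 50% to 100% range for the PARA illustrates how often the baseline could be late under assumed dates; it does not measure bias. The point still merits a change to the protocol, because the remedy is cheap and the lost observation cannot be replaced.

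**What to change.** - In section 2.10, define the baseline PARA and the outdoor part of the NAP SACC as taken before any garden siting or build work at the centre. Use the same lead time before programming at Child Safety centres.
- Record the build date at each centre.
- Flag any baseline taken after the build, and repeat the baseline-to-post comparison without those centres as a sensitivity analysis.

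Comparing post-intervention scores alone is not a good substitute. With 24 centres it gives up control for initial differences between them.

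The cost is a sentence or two in the protocol and a slightly earlier visit; the PARA itself takes about 10 minutes. The downside is a somewhat longer gap between baseline and the start of programming.

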### 2.11. Other Assessments

Meeting minutes and field notes will be maintained to document concerns about sustainability raised by the CAB, parents, ECEC directors, and teachers. These can be triangulated by level and extent of replicability and institutionalization to qualitatively examine the relationship between sustainability and child outcomes.

Cost to deliver the intervention is estimated in constant dollars using the Prospective Payment System Input Price Index [49]. This index examines (1) costs of identifying and recruiting participants, including ECEC staff, (2) direct intervention labor costs, including teachers’ time, (3) personnel recruitment and training costs, and (4) material and supply costs (e.g., printed material, garden supplies). Care will be taken to accurately separate research-based costs from replication or implementation costs [50]. A cost-to-deliver spreadsheet will be created to abstract information from production of supplies; receipts from supplies; and times for training, delivery, and administration weighted by employment cost. Costs can be factored per participant to determine a cost to deliver the intervention for each participant.

## 3. Discussion

This paper describes the SAP model and process for improving the sustainability and institutionalization of the SAGE program. There are few existing, comprehensive, and theoretically-guided strategies to evaluate sustainability in ECE programming that can be linked to Sustainable Development Goals put forward by the World Health Organization, following the United Nations’ lead, such as improving nutrition and helping to eliminate preventable disease [51]. Gardens and garden-based curricula, if sustained by ECE sites, may help to contribute to a multilevel systems approach to attaining these goals. The SAP is theoretically guided using the EMO [31], an ecologic framework guiding intervention planning and measurement at multiple levels of analysis. The SAP was conceived using sustainability constructs developed during the multi-site and multi-level CORD trial [10]. The result is a comprehensive mixed methods analysis plan relying on both observed and self-reported data, to determine the potential for sustainability of SAGE, a garden-based physical activity and nutrition intervention to prevent obesity in young children linked to best practices and policy for ECECs [34,36].

This study proposes to measure the depth of implementation of various elements of the customizable SAGE curriculum to determine what is sustained, or expanded upon in future iterations of the programming. A strength of providing a customizable curriculum for sustainability is that *replicability* is enhanced [2]. This is particularly important for underserved populations and low-income areas, where resources for delivering evidence-based interventions may be limited. Giving teachers supportive sustainability strategies to access a variety of virtually no cost games, learning opportunities and songs, and low-cost science experiments coupled with the boon of experiential learning provided by a garden is helpful for increasing replicability and scalability. These activities are simple to do, and the addition of a website with instructions, printable materials and video demonstrations can provide opportunities for teachers to pick and choose the activities that they prefer with on demand support available. Future sustainable development of SAGE could include resources to deliver the curriculum in other languages, enhancing access to sustainable learning opportunities for scaling-up SAGE to be offered internationally.

There are few studies about dissemination and implementation research in order to sustain physical activity and nutrition, garden-based programming in ECECs [25,26,52,53,54]. This study is innovative in that it plans for anticipated barriers based on the experience of a CAB as well as a review of the scientific literature [34,35,36], and includes strategies to measure implementation at multiple levels of analysis guided by the EMO [28,29,31]. The inclusion of a knowledgeable scientific team with experience working with, developing, and operationalizing sustainability constructs suitable for measurement in ECEC sites and in connected pathways [1,2,10].

The *continuation of benefits*, from the school to the home, is an important element that should be captured as part of all implementation and sustainability programming [2]. Parent engagement is an important area for improvement in most ECE and school-based intervention programming, including SAGE, which is dependent on communication with parents and families of the child [54]. Although ECECs provide important learning opportunities that young children might not be able to obtain at home, a second important role of these sites is that they are a safe place for parents to leave their young children while they are at work. Measuring parents’ perceptions of outreach materials (i.e., newsletters) is another strength of this study to assess the potential for *continuation of benefits*.

Since the SAGE SAP is comprehensive, one potential limitation is the high intensity of the labor involved to collect information from numerous data sources. This level of intensity can discourage adoption by ECEC personnel and impede *institutionalization* of the programming itself [10]. As previously discussed, even the most carefully crafted plans for evaluation can be derailed by competing priorities (e.g., changing educational policy priorities; teacher strikes) and forces of changes (e.g., pandemics; telecommunication interruptions) [2]. Strong *community capacity*, defined by including a CAB and investing in high ECEC site engagement, provides the ability to seek counsel and resources to support flexibility to pivot to strategies that may be more helpful for implementing programming and completing assessments, such as using online surveys or virtual platforms (e.g., Zoom). In addition, encouraging ECEC personnel to take pictures of site successes (e.g., happy children, thriving garden) and struggles (e.g., garden pests, broken or overused supplies) is another strategy to help enhance sustainability of various elements of the curriculum. These pictures are also a great way to keep study sites connected on social media to strengthen the community support for garden-based programming. Strong communication and good relationships with community partners and on-the-ground implementers is extremely important for improving adoption as well as sustainability [55].

